## Abstract

**Background:**

Even though a high demand for sector spanning communication exists, so far no eHealth platform for nephrology is established within Germany. This leads to insufficient communication between medical providers and therefore suboptimal nephrologic care. In addition, Clinical Decision Support Systems have not been used in Nephrology until now.

**Methods:**

The aim of NEPHRO-DIGITAL is to create a eHealth platform in the Hannover region that facilitates integrated, cross-sectoral data exchange and includes teleconsultation between outpatient nephrology, primary care, pediatricians and nephrology clinics to reduce communication deficits and prevent data loss, and to enable the creation and implementation of an interoperable clinical decision support system. This system will be based on input data from multiple sources for early identification of patients with cardiovascular comorbidity and progression of renal insufficiency. Especially patients will be able to enter and access their own data. A transfer to a second nephrology center (metropolitan region of Erlangen-Nuremburg) is included in the study to prove feasibility and scalability of the approach.

**Discussion:**

A decision support system should lead to earlier therapeutic interventions and thereby improve the prognosis of patients as well as their treatment satisfaction and quality of life. The system will be integrated in the data integration centres of two large German university medicine consortia (HiGHmed (highmed.org) and MIRACUM (miracum.org)).

**Trial registration:**

ISRCTN16755335 (09.07.2019).

## Background

The digitization of medicine will fundamentally change access and links to health and disease data over the next few years. Nephrology patients are a particular interesting subpopulation as a use case with a large body of medical data since both children and adults with chronic renal insufficiency suffer from secondary (or primary) diseases of other organ systems. In addition, in the large population of patients undergoing dialysis therapy, there is considerable generation of data from renal replacement therapy or transplantation and its follow-up, as well as from the complex medication requirements.

In Germany, patients with chronic kidney disease are generally treated on an outpatient basis by (pediatric) nephrologists in private practices or in other outpatient care institutions, e.g. the Kuratorium für Dialyse und Nierentransplantation (KfH), the Patientenheimversorgung (PHV), or Davita, Nephrocare, BBraun and others. In addition, many patients have comorbidities or intercurrent conditions, treated by general practitioners / ambulant pediatricians. However, records are typically kept in separated IT systems. Various software systems exist in the outpatient GP setting, but in the nephrological context data documentation is usually (> 90%) via the GP information system Nephro7. Nephrology patients often require inpatient care (e.g. due to dialysis [access] problems, infections, transplants, transplant complications, other comorbidities). This is usually provided in nephrology departments at Hannover Medical School (MHH) (Hannover Metropolitan Region) and Klinikum Siloah (Klinikum Region Hannover). Here, in the two Hannover-based hospitals, data are documented within the hospital information systems using SAP-ISH-med using the electronic medical record ISH-med by Cerner. In practice today, patient information between the different sectors of the health system are only exchanged through paper reports or phone calls. This leads to information and data losses and thus to a quality deterioration in the medical treatment of (pediatric) nephrological patients. The intelligent support of patient care within a multi-stakeholder environment through decision support systems, as well as quality management and comparison between different regions, is therefore currently not feasible.

In other countries, it has already been demonstrated that digitization of nephrology data can lead to better patient care [1–3]. Apart from our regional kidney transplant project KTX 360° [4], funded by the Innovation fund of the Joint Committee (G-BA) of the Federal Republic of Germany (www.ntx360grad.de), no eHealth networks in nephrology have yet been established in Lower Saxony or Germany as a whole. Within this project, initiated in 2017, several steps have been made towards eHealth systems for the subpopulation of patients with kidney transplants. In cooperation with Symeda GmbH, a small Braunschweig-based company, a cross-sectoral communication platform for kidney transplants was established, serving more than 50 participating (pediatric) nephrologists in Lower Saxony and the KTX Center Hannover Medical School. This platform is additionally used for the exchange of structured medication plans, documents in PDF format, and individual laboratory values. It further enables teleconsultations [4]. The first steps towards interfacing with the Nephrology GP system Nephro7 have also been established. An interface with a hospital’s electronic medical record system has, however, not yet been established [5]. General practitioners and pediatricians in Germany use a large variety of different commercial software systems, so that implementing interfaces to all such systems would not be reasonable. For them, the most important functions would be login access to medical data of patients treated by them and a chat function for teleconsulting.

Within the German Federal Ministry of Education and Research (Bundesministerium für Bildung und Forschung [BMBF])-funded HiGHmed consortium [6], a new approach to enable data sharing and intelligent computing of electronic health records and research data collections is currently being implemented through components of data integration centres established at eight German university hospitals [7]. The long-term vision for HiGHmed is to develop a joint technology platform across all university hospitals and research units that will assist and promote data-based knowledge-building and decision-making processes in patient-centered diagnostics, treatment and care. This includes profiling these standards and agreeing on common semantics for real-life implementation. Data that is integrated using the HiGHmed Platform shall strictly fulfil the FAIR principles of data sharing [8]. This means, that the envisioned architecture makes all relevant data findable, accessible, interoperable and reusable if the patient has given his or her consent.

Through consequent use of open system architectures, open data models and open application programming interfaces (e.g. Integrating the Healthcare Enterprise [IHE], openEHR and Fast Healthcare Interoperability Resources [FHIR]), the “FAIR”, vendor neutral and extensible health data platform will provide the means to enable and promote research collaboration and re-use of data collections and allow the seamless sharing of data between clinical applications and research databases. This open approach shall prevents the data from becoming locked in proprietary databases. Thereby the data within a patient’s electronic health record can finally outlast ephemeral software products whose lifecycle (10–15 years) is normally significantly shorter than the average life expectancy of a human.

Through the development and use of open, standardized and computable domain models, data becomes accessible to algorithmic processing, analytics and process management. This is the prerequisite for any intelligent reuse of the data. Based on the main platform components of HiGHmed, the first projects using artificial intelligence and machine learning have been conducted at MHH, i.e. a decision-making system in pediatric intensive care medicine was developed and the application of openEHR archetypes helped to bridge the interoperability gap between local infrastructures and a decision support system in a prototype implementation [9].

Using the same technical and semantic foundation, the incorporation of a clinical decision support tool within a regional health network in Sweden has shown significant improvements regarding the adherence to guidelines on anticoagulant therapy in patients with atrial fibrillation at risk of stroke [10].

The reference architecture will be scalable and open for adoption by additional partner hospitals, as well as for many solution developers, to provide innovative applications, e.g. for data integration or analytics. Therefore, HiGHmed provides an platform ecosystem for integrating electronic medical record systems, GP office software and the KTX 360° health information exchange platform to be used for all regional nephrology patients [7, 8, 11, 12]. MIRACUM [13] is a second large consortium (comprising ten German university hospitals) funded in the German medical informatics initiative [14]. The university hospital in Erlangen, is coordinating the MIRACUM project and is therefore the ideal partner in our project with the goal to create an interoperable IT-solution that is feasible for most university hospitals in Germany.

The underlying platform of NEPRHO-DIGITAL will further provide patient access to important data and thus lead to a significant improvement in the treatment of (pediatric) nephrological patients by providing easy retrieval of important data or teleconsulting for all physicians involved. From a future perspective, this system could be transferred to other MHH-based specialist treatment settings, establishing constant data sharing with ambulant care providers, optimizing quality of care.

Due to the distribution of data in different IT systems, there has been no machine learning of prediction models from routine nephrologic data until now and it has not been possible to compare treatment quality between different regions.

## Methods/design

Within the framework of the project NEPHRO-DIGITAL the functions of the existing KTX360° health information exchange platform, are to be extended for non-kidney transplanted nephrology patients to support the care of all types of (pediatric) nephrology patients. These include automatic comparison of dialysis treatment data, the transfer of laboratory data, diagnoses, and comorbidities, as well as other patient information. An automatic exchange of the so called ‘German federal consistent’ medication plan and all laboratory values between physicians should be achieved using this enhanced Health platform. It is our goal that in its final deployment stage the platform shall fully replace paper reports exchanged between doctors and also include data that is generated by the patients themselves. For acquiring a second opinion, teleconsultations between the service providers in the different health care sectors can take place at any time via the system. We aim to develop and evaluate an open standards-based approach for establishing a CDSS upon this platform with an exemplary system for automated prognosis of kidney function and the development of cardiovascular disease in nephrology patients (Fig. 1). This will permit retrieval of dynamic facts in a standardized and unambiguous form to facilitate clinical decision support in this complex area with the goal of detecting patients with worsening renal function or cardiovascular comorbidity early enough for therapeutic intervention. We further aim to compare treatment data between the Hannover and Erlangen/Nürnberg regions in order to show possible differences in treatment quality and thus identify how nephrological care can be improved. At its end this will also serve to assess the transferability of our technical approach.

**Fig. 1 Fig1:**
[figure not shown]
Structure of NephroDIGITAL

### Hypothesis

The primary hypothesis underlying the project is that the digitization of nephrology data and processes presented above will result in a significant improvement in patient care and, in addition, will lead to cost savings in the health care system by reducing hospitalization and redundant diagnostics (hospital, nephrologist, general practitioner/pediatrician) and treatment and by improving quality of life.

### Working plan

The planned digitization of nephrology can only be achieved in an interdisciplinary team. The medical basis for the necessary structure of the eHealth platform is derived from (pediatric) nephrology whereby (pediatric) nephrologists, pediatricians and general practitioners, together with patients, will be the primary users of the new digital nephrology. The evaluation of the use of the new regional nephrological digital network will be carried out by a health scientist.

The CDSS to be developed can serve as a blueprint for future artificial intelligence systems that can be implemented in other health networks in order to improve care. As the applications built as part of this project use the HiGHmed platform infrastructure based on open interoperability standards that can interface that of the German Telematik infrastructure, our system will also be ready for use in different regions. With the inclusion of interfaces to the most commonly used IT system within German hospitals (MHH and Klinikum Region Hannover: SAP-ISH-med) our eHealth platform will be ready for use in the majority of hospitals. Making the eHealth platform also interoperable with the MIRACUM data integration centre concept implemented at Erlangen University (and at nine other German university hospitals) will ensure that our eHealth platform will be compatible with the architecture of most German university hospitals.

#### General practice: assessment of needs, acceptance, feasibility in GP/pediatric care

Relevant information and exchange tasks for primary care providers (GPs, pediatricians) will be identified. Feasibility aspects will be assessed multiperspectively and longitudinally using mixed methods of health service research (qualitative/quantitative) to elucidate barriers and facilitators for acceptance and use. Subsequently, the eHealth platform shall be adapted to identified stakeholder needs in order to warrant its use in the ambulant care sector. Further, this may act as a use case for technical interfaces to improve cross-sectoral cooperation with primary, secondary and tertiary care in other specialties.

Objectives:
To identify data, information and exchange needs of primary care providersTo assess barriers and facilitators for eHealth platforms use in primary care providers

Qualitative Methods: Interviews with key stakeholders (GPs, Hausärzteverband) (t0, t1), survey, final workshop/focus groups.

#### Nephrology

Nephrologic parameters for the eHealth platform will be defined and standardized between the caregivers participating in the project. The implementation of the eHealth platform into routine care will be organized and adapted to the needs arising within the project. A main task for the physician executing SP2 will be the constant communication with the caregivers within both tasks with the goal of achieving high acceptance of the eHealth platform. In addition, the parameters for the the patients´ data provision into the eHealth platform will be developed together with the patient organizations in order to create a tool that will be widely used for nephrology patients. The nephrologist will also be responsible for the medical aspects of developing and implementing the CDSS.

#### Semantic interoperability, data integration and predictive modeling

The semantic information models describing the data items required within the domain of nephrology will be defined. These models will serve as defined semantic models that can be used for multiple purposes, including the definition of data capture forms in electronic health records communication interfaces, database schemas, data validation algorithms, data querying, etc. The creation of the domain models will be closely aligned to the modelling activities in HiGHmed, the openEHR Foundation and related SDOs (standards developing organizations) such as HL7 and IHE. Based on the representation of the data within the open platform, machine learning and data analytic algorithms will be developed that allow distributed computing of the data, permitting privacy preserving use of data from the deployments of the Hannover and Erlangen platforms.

#### Advancement of the eHealth platform

The goal of this subproject is to further develop the eHealth platform with regards to the needs of patient care in the nephrology setting. The architecture will be based on the findings of the HiGHmed project and therefore builds up the base for semantic interoperability. This is the prerequisite for big data analytics in health care. By 2021 all German health insurance companies will be obliged to offer apersonal electronic health record to their customers. This will provide the perfect infrastructure for NEPHROLOGIE-DIGITAL (NEPHRO-DIGITAL), because the eHealth platform will offer basic services, such as authentication, security and medication history. On the other hand, these systems will not implement the needs for specialized medical fields, such as nephrology. Symeda will ensure that NEPHRO-DIGITAL will be compliant with the German telematics innfrastructure requirements.

#### Interface and establishment of NEPHRO-DIGITAL in the Erlangen / MIRACUM network

To demonstrate transferability of the concept the regional networks in southern Germany with the University Hospital of Erlangen (UKEr) will be used. Erlangen is participating in patient recruitment within the KTx360° program and thus uses the identical eHealth platform and an adapted network with private practices and regional dialysis providers. Moreover, UKEr is part of the German medical informatics MIRACUM consortium. One of the aims of MIRACUM is to establish data integration centers that will be embedded in the hospital IT infrastructure and can facilitate the collection and exchange of data within the consortia university hospitals. Thusm NEPHRO-DIGITAL could emerge as a common use case between MIRACUM and HiGHmed to illustrate interoperability between both BMBF-funded initiatives, creating a first state- and sector-spanning care and research platform in Germany.

##### Evaluation

Evaluation is planned and carried out based on S.M.A.R.T. (specific, measurable, attainable, realistic and timely) criteria. Here, health data of the patients (from the eHealth platform, as well as from the nephrology GP system and the hospitals EMR) in the project, as well as of historical control patients, must be extracted, exported and analyzed in cooperation with MHH biometry resources.

S.M.A.R.T. criteria:

**A** Evaluation of care provider needs on data and information sharing, acceptance and feasibility (qualitatively, interviews with GPs / pediatricians) at 30 months.

**B** Implementation of a cross-sector eHealth platform including teleconsultations and patient access. Indicator: 50% of patients with shared use of the platform after 30 months.

**C** Implementation of a decision support system for GFR deterioration and cardiovascular comorbidities. Indicator: System is implemented at 30 months.

**D** Comparison of intersectoral treatment quality between Hannover Region and Erlangen. Indicator: Analysis performed at 30 months.

**E** Reduction of complications of nephrological diseases. Indicator: Reduction of complications requiring inpatient treatment. Indicator: A 10% reduction of hospital expenditure within 30 months compared to a control cohort (historical control patients who did not participate in the program).

**F** Reduction in cardiovascular events. Indicator: The number of hospitalizations due to cardiovascular events will be reduced > 10% within 30 months.**G** After the establishment of NEPHRO-DIGITAL, participant quality of life will improve significantly. Indicator: In the mental subscale of the SF-12, 80% of the participating patients will reach values which do not differ from population norm data within 30 months.

**H** Is the use of the new digital elements and the quality of life gender-dependent? Does a migration background play a role in the acceptance of digital medicine? Indicator: Participation rate in subgroups is not significantly different after 30 months.

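### Criterion G claims that quality of life improves, but its only indicator is a level reached against population norms, with no baseline, change or comparator

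*Protocol article*

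**What the plan says.** The Evaluation section of the protocol article lists eight S.M.A.R.T. criteria, A to H. Criterion G opens with its aim: "After the establishment of NEPHRO-DIGITAL, participant quality of life will improve significantly". One indicator follows. The instrument is given by "In the mental subscale of the SF-12", and the success rule is that "80% of the participating patients will reach values which do not differ from population norm data", with a horizon of 30 months.

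The indicator mentions no SF-12 value at entry, no change score and no comparison group. Criterion E, two items above, does name a comparator for hospital expenditure: "compared to a control cohort (historical control patients who did not participate in the program". G has no such clause.

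Quality of life also appears in the Hypothesis section. The primary hypothesis expects better patient care and lower costs, the latter in part "by improving quality of life". Criterion H asks whether quality of life depends on gender, but its indicator is a participation rate. G is therefore the only criterion whose indicator measures quality of life.

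**The concern.** The aim of G is a statement about change. The indicator is a statement about where patients end up relative to an external reference. The two coincide only if the share in the norm range at entry is known, and the indicator does not use it.

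Two wrong conclusions become possible. A cohort that enters with most patients already in the norm range meets the 80% target with no change, or even after a decline. A cohort that enters well below the norm and truly improves can still fall short of 80%.

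The Discussion section makes introduction into routine care depend on confirming the project's positive effects. A criterion that can be met without an effect, or missed when there is one, is a poor basis for the quality-of-life part of that decision.

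**Working it through.** **Set the two sentences of G side by side.**

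| Element | Aim of G | Indicator of G |
|---|---|---|
| Type of claim | change (improvement) | level reached |
| Reference | implicitly, the patient's own earlier state | population norm |
| Baseline used | needed | none |
| Comparator | none named | none named |
| Threshold | significance | 80% of patients |

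The mismatch is visible from the text alone and needs no assumption.

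**How much it can matter.** The article gives the 80% target without a derivation, so there is no figure to reproduce. It gives no SF-12 mean, SD or entry level for these patients, so the following is illustration only.

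Assumptions: scores are normal; the norm has mean 0 and SD 1; patients have mean −d (a deficit of d norm SDs) and SD r. The base case is r = 1, with r = 0.8 and r = 1.2 as a range. Φ is the standard normal distribution function.

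*Reading A: not differing means within ±1.96 norm SD.* Share = Φ((1.96 + d)/r) − Φ((−1.96 + d)/r). With r = 1:
- d = 0: Φ(1.96) − Φ(−1.96) = 95.0%
- d = 0.5: Φ(2.46) − Φ(−1.46) = 92.1%
- d = 1: Φ(2.96) − Φ(−0.96) = 83.0%
- The share falls to 80% at d ≈ 1.11.

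A cohort that declined from the norm to a full SD below it would still meet the target (95.0% to 83.0%).

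*Reading B: not differing means no lower than norm minus 1 SD.* Share = Φ((1 − d)/r). With r = 1:
- d = 0: Φ(1) = 84.1%
- d = 0.2: Φ(0.8) = 78.8%
- d = 0.5: Φ(0.5) = 69.1%
- The share equals 80% when 1 − d = 0.842, so d ≈ 0.16.

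A cohort that improved from 0.5 SD to 0.2 SD below the norm, a gain of 0.3 SD, would move from 69.1% to 78.8% and miss the target.

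**Sensitivity to the patient SD.**

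| | r = 0.8 | r = 1.0 | r = 1.2 |
|---|---|---|---|
| Reading A, d = 0.5 | 96.5% | 92.1% | 86.8% |
| Reading A, d = 1 | 88.5% | 83.0% | 78.1% |
| Reading B, d = 0 | 89.4% | 84.1% | 79.8% |
| Reading B, d = 0.5 | 73.4% | 69.1% | 66.1% |

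The percentages move with r, and at r = 1.2 the cohort 1 SD below the norm just misses the target under Reading A. The pattern stays: under Reading A a cohort 0.5 SD below the norm meets the target at entry for every r shown, and under Reading B it does not. Under neither reading does the share say whether anyone improved.

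**The case against.** The strongest objection is that a journal article need not say how a single patient's score is judged against the norm. The norm table, the age and sex strata and the cut-off commonly stand in the full protocol or the analysis plan, neither of which is shown. That stands. The missing cut-off is not itself a defect, and the percentages above show only how the indicator would behave under particular definitions. It does not rescue G, however. Any cut-off yields a share at a level, and making it measure change would require a different indicator from the one stated.

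A reader might go further and infer that the 80% target is either automatic or unattainable. The documents do not support that. Those are the extreme readings; Reading B is demanding but reachable. Even under a narrow band of ±1 norm SD, where 68.3% of a cohort identical to the norm population would qualify, 80% is not ruled out. A cohort centred on the norm reaches it if its SD is about 1/1.2816 = 0.78 of the norm SD.

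A reader might also infer a formal test at one visit, or that patients scoring better than the norm count as failures. The article describes no test and names no visit; its horizon could mean any time up to month 30. Its verb suggests attainment from below. Counting attainment at any time would make the target easier and would still measure no change.

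One could say that reaching the norm implies improvement. It would if only patients below the norm at entry were counted, but the denominator is all participating patients.

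Finally, G is one of eight project criteria, some of them plain milestones. It is not named as a primary endpoint, and the article bases no sample size on it. That is fair and limits the severity.

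**Conclusion.** The point holds in this form: G's aim is improvement, its sole indicator is attainment of a population norm, and without a baseline, change or comparator the indicator cannot show whether the aim was met. This follows from the text and does not depend on how the norm range is defined.

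The size depends on inputs the article does not give. With normal scores and equal SDs, 92% of a cohort 0.5 SD below the norm qualify at entry under the ±1.96 SD reading, and 83% of one 1 SD below. Under the one-sided 1 SD reading, 84% qualify at no deficit and 80% at a deficit of 0.16 SD.

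It would be too strong to say that G yields no information on quality of life. A level compared with norms is descriptive evidence, but not evidence of improvement. The point should be fixed; it is not fatal to the evaluation.

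**What to change.** 1. Collect the SF-12 at platform activation for every participating patient. A baseline not taken then cannot be recovered later.
2. Make the indicator of G the within-patient change in the SF-12 mental score from activation to 30 months, reported with a 95% confidence interval. Claim improvement only if the interval lies above zero. A mixed model for repeated measures is one suitable way to estimate the change; others would serve.
3. Keep norm attainment as a descriptive result at both baseline and follow-up, with an explicit one-sided cut-off so that scores above the norm count as attained.
4. State that an uncontrolled before-after change does not by itself attribute improvement to the platform, since regression to the mean and time trends remain possible explanations.

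The cost is a rewording of G and one extra 12-item form per patient. The remaining limitation is the one in item 4: the revised indicator measures what G claims, but not its cause.

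### Criterion H asks about use, acceptance and quality of life by subgroup, but its only indicator is an undefined participation rate, so it can be met while these differ

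*Protocol article*

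**What the plan says.** The Evaluation section of the protocol article lists criteria A to H, most of them with an indicator. Criterion H poses two questions. The first is "Is the use of the new digital elements and the quality of life gender-dependent", which covers both use and quality of life. The second is "Does a migration background play a role in the acceptance of digital medicine". One indicator follows for both: "Indicator: Participation rate in subgroups is not significantly different after 30 months". The article does not say what participation rate means.

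Three other criteria bear on the wording:

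- B, on implementing the platform, has its own measure of use: "Indicator: 50% of patients with shared use of the platform after 30 months". It is not split by gender or migration background.
- E describes its control cohort as "historical control patients who did not participate in the program".
- G sets its quality-of-life target on the SF-12 mental subscale: "80% of the participating patients will reach values which do not differ from population norm data within 30 months". It is not split by gender.

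**The concern.** H names three outcomes (use, quality of life, acceptance) and measures a fourth. If participation means being in the program, equality of participation says nothing about whether men and women, or patients with and without a migration background, use the platform to the same extent once they are in it. A language or usability barrier that appears after joining would not show in the indicator.

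No other criterion closes the gap. B measures use only overall. A covers needs, acceptance and feasibility, but among general practitioners and pediatricians, not patients. H is the only criterion that looks at gender and migration background at all. A favourable result could therefore be read as evidence that digital care reaches these groups equally, when use was never compared.

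**Working it through.** **No stated figure to reproduce.** For H the article gives no sample size, subgroup sizes, expected rates or significance level. The check is a comparison of wording, followed by an illustration on assumed figures.

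**Step 1. Questions against measures (Evaluation section).**

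| Quantity in H's questions | Measured by H's indicator? | Measured elsewhere? |
|---|---|---|
| Use of digital elements, by gender | Only if participation means use | B: shared use, overall only |
| Quality of life, by gender | No, under any reading | G: SF-12 mental subscale, overall only |
| Acceptance, by migration background | Only if participation stands for acceptance | A: acceptance among primary care providers, not patients |

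**Step 2. What participation most naturally means.** E applies the verb to taking part in the program. G applies the participle to the patients whose quality of life is assessed. B uses a different term for use and sets it at 50%, so not every patient is expected to be a shared user. Together these favour reading participation as being in the program. This is an inference from usage, not a definition in the text.

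**Step 3. What follows on that reading.** For subgroup *i*, let *p_i* be the participation rate and *u_i* the share of participants who use the platform. Use among all patients of the subgroup is *p_i × u_i*. H compares *p_1* with *p_2*; *u_1* and *u_2* do not enter. With *p_1 = p_2 = p*, the gap in use is *p(u_1 − u_2)*. It is zero if use among participants is equal and can be large if it is not. The indicator gives the same answer in both cases.

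**Step 4. Illustration of H alone (all inputs assumed).** Participation is 60% in both subgroups. Use, on the same base of all patients in the subgroup, is 42% and 30%, which is 42/60 = 70% and 30/60 = 50% of participants. The test is the pooled two-proportion z-test, two-sided:

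z = |a − b| / √[p̄(1 − p̄)(1/n₁ + 1/n₂)]

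For N = 500 split 50:50, p̄ = 0.36 and z = 0.12 / √(0.36 × 0.64 × 2/250) = 0.12 / 0.0429 = 2.80, so p = 0.005.

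| Total N | Split | p, participation 60% v 60% | p, use 42% v 30% |
|---|---|---|---|
| 200 | 50:50 | 1.00 | 0.077 |
| 200 | 80:20 | 1.00 | 0.165 |
| 500 | 50:50 | 1.00 | 0.005 |
| 500 | 80:20 | 1.00 | 0.028 |
| 1000 | 50:50 | 1.00 | 0.0001 |
| 1000 | 80:20 | 1.00 | 0.002 |

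The indicator is met in every row. The 12-point gap in use would be significant at 500 and 1000 patients, but not at 200.

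**Step 5. Illustration of H and B together (all inputs assumed).** Participation is equal in the two subgroups, and shared use is taken among enrolled patients.

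- Equal subgroups: (62 + 38)/2 = 50%, gap 24 points.
- Equal subgroups: (55 + 45)/2 = 50%, gap 10 points.
- Equal subgroups: (70 + 30)/2 = 50%, gap 40 points.
- Split 80:20: 0.8 × 55 + 0.2 × 30 = 44 + 6 = 50%, gap 25 points.

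H and B give the same result in all four. The figures were chosen to sit on B's target. They show that the two indicators cannot see the gap, not how large it is likely to be.

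**The case against.** The strongest objection is that participation rate is undefined and directly follows questions about use and acceptance, so it may mean taking part in the digital elements. Measured after 30 months, it may also mean still taking part then. E describes historical controls and G is no more precise than H, so neither defines the term. The article condenses a fuller document, where numerator and denominator would normally be set out.

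Part of this stands. A reader might infer that patients who join and never use the platform, or stop using it, count as success under H. The article does not support that. It never says such patients are counted as participants, and the 30-month timing could exclude those who left the program (though not those who stay in it without using the platform). Nor can an individual non-user be a success: H is met or not met at group level, and non-use hides a difference only if it is unequal between the subgroups.

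It is also fair that B's shared use may mean use across several providers rather than the patient's own use, that the article does not mention usage logs, and that the Discussion does not make the move to routine care depend on H. The General practice section plans work on barriers and facilitators, and the Nephrology section develops patient data provision with patient organizations. The former concerns primary care providers, and neither compares patient use by subgroup.

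The objection does not remove the mismatch. A definition left to a fuller document is not the complaint. The article does state H's indicator, and it names a different quantity from its questions. If active use was intended, H should say so. The missing quality-of-life measure depends on no reading of participation.

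**Conclusion.** The concern holds in a limited form. H's indicator does not measure what H asks. For quality of life by gender this follows from the text alone. For use and acceptance it rests on reading participation as being in the program, which the wording of B, E and G supports but does not prove. On that reading H can be met whatever the subgroup gap in use, provided participation is similar.

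The size cannot be derived from the article. The gaps of 10 to 40 points are illustrations on assumed rates and do not predict what the trial will find. H is one of eight evaluation criteria, so this affects one conclusion, not the whole evaluation. It should be corrected because no other criterion examines these subgroups.

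Whether a non-significant difference is an adequate way to show equality is a separate question and is not needed for this conclusion.

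**What to change.** Make H's indicator patient use of the platform at 30 months, by gender and by migration background. The denominator is all enrolled patients of each subgroup, and patients who never used the platform or stopped using it count as non-users. Take it from the patient-level use data that B needs. If B's shared use means use across providers, state that H refers to the patient's own use; in that case, confirm that the platform data record it.

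For the quality-of-life question, report by gender the SF-12 mental subscale already collected for G. Keep participation rate as a separate, defined descriptive figure, because a denominator of enrolled patients does not show who failed to enrol.

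The cost is a change of wording and one extra tabulation, plus a breakdown of SF-12 data already held. H may look less favourable than under the participation indicator.
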